**Methods and analysis:**

The Observing a Decade of Yearly Standardised Surveillance in EVAR patients with Ultrasound or CT Scan study comprises a national multicentre retrospective cohort study in 17 medical centres. Consecutive patients with an asymptomatic or symptomatic infrarenal AAA who underwent EVAR between January 2007 and January 2012 will be included in this study with follow-up until December 2018. Clinical variables and all follow-up information will be retrieved in extensive data collection from the patient’s medical records. In addition, an e-survey was sent to vascular surgeons at the 17 participating centres to gauge their opinions regarding the possibility of safely reducing the frequency of imaging surveillance. Primary endpoints are intervention after EVAR and aneurysm-related mortality. The initial estimated sample size is 1997 patients.

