**Figure 1 F1:**
[figure not shown]
Patient subgroups. AAA, abdominal aortic aneurysm; CTA, CT angiography; EVAR, endovascular aneurysm repair.

The standard of care is defined by the current guidelines and IFU. The usual follow-up schedule in the IFU is: CTA and abdominal X-ray at 30 days, 6 and 12 months and yearly thereafter. The 2019 ESVS guidelines recommend a CTA 30 days after EVAR. If there is adequate seal and no endoleak, patients are classified as low risk and CTA follow-up may take place 5 years later. If there is an inadequate seal and endoleak type I/III patients could be either evaluated for re-intervention or if sac shrinkage occurs yearly DUS is recommended. In the 2018 SVS guideline, CTA at 1 and 12 months is recommended and if neither endoleak nor sac enlargement is documented, DUS is suggested for annual postoperative surveillance. In our study design, the definition of compliance is undergoing imaging surveillance every 16 months since patients in most centres will be rescheduled if they missed their annual follow-up visit. Device-specific complications after EVAR will also be examined.

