### Study procedures

The primary outcomes of this study are interventions and aneurysm-related mortality for patients who had a normal initial postoperative CTA and who do adhere to our definition of yearly imaging surveillance over a 6-year to 11-year follow-up period, compared to those who do not adhere to our definition.

Interventions are EVAR-related interventions defined by the SVS reporting standards as postoperative adjunctive manoeuvres.^16 17^ Interventions for wound complications at the access site are not included, since these are detectable without the use of imaging.

Date of death during follow-up, if applicable, will be obtained from patient medical records and verified by the Dutch municipal personal records database (GBA).

Details of all surveillance imaging are obtained from patient medical records and radiology reports. The time between imaging appointments is calculated to determine whether patients adhere to this studies definition of with yearly imaging surveillance, that is, within every 16 months.

Date, type, indication and outcome of all postoperative imaging during follow-up are obtained from patient medical records, specifically imaging order forms and radiology reports. A normal initial postoperative CT scan is defined as a CT scan which shows no endoleaks, endograft migration (>10 mm), kinking or obstruction. All imaging outcomes are based on the report compiled by radiologists. These reports will not be re-evaluated by an independent radiologist, since we want to base our outcomes on real life data.

Secondary outcomes are all-cause mortality, type I, type II, type III and type IV endoleak, graft or outflow (iliac) occlusion, aneurysm rupture and endograft infection. This is also obtained from patient medical records, specifically radiology reports and Dutch municipal personal records database (GBA).

Date of aneurysm rupture is obtained from patient medical records, specifically operative reports, radiology reports and progress notes.

Costs of all EVAR-related imaging and outpatient clinic visits will be calculated per patient. Cost is defined as volume times price. Prices from the ‘Cost manual of the Dutch Health Care Institute’’ will be used. Costs for the patients will also be included. The quality-adjusted life years, a generic measure of disease burden including both the quality and quantity of life, cannot be calculated with this retrospective design.

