## Discussion

The goal of this study is to evaluate whether a reduction in follow-up visits and imaging and thus costs, in patients operated on for an asymptomatic or symptomatic AAA with EVAR is safe. We hypothesise that there will be less interventions and no difference in aneurysm-related mortality in patients with less intensive follow-up. With the results of this study, we aim to provide scientific evidence helping vascular surgeons decide whether less vigilant follow-up after EVAR may be considered for patients classified in the low risk group.

The strengths of the ODYSSEUS study are that it can accumulate the data of a large number of consecutive EVAR patients with a theoretical follow-up of 6 to 11 years, and that it captures all surveillance visits, long-term outcomes and mortality post-EVAR. Moreover, 17 medical centres throughout the Netherlands are participating in this study, including university and general hospitals, thereby reducing selection bias.

An e-survey has been sent to all vascular surgeons participating in the ODYSSEUS study. This shows that yearly imaging surveillance is upheld by most vascular surgeons in the Netherlands. In addition, most physicians agree that yearly imaging frequency can be safely reduced in a specific group of EVAR patients. As support for this reduction in frequency is evident in the Netherlands, the next step will be to study the groups for which it will be safe to deviate from the widely accepted surveillance protocols.

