Our study is subject to limitations due to the nature of administrative data and its retrospective and observational design. As with all studies using administrative data, it allows only the collection of data that was documented in patient medical records. It is also possible that some patients may have transferred to alternative surveillance protocols in different medical centres without our knowledge. The study will assess results in 17 medical centres over 11 years, during which time improvements in endograft and in clinical practice has occurred. Attrition bias due to loss to follow-up represents a threat to the internal validity of our cohort study. The mentioned e-survey has only been sent to participating vascular surgeons, perhaps surgeons participating in the ODYSSEUS study strongly believe that imaging surveillance frequency can be reduced. This may have provided a biased view of post-EVAR follow-up in the Netherlands. However, most of the high-volume EVAR centres in the Netherlands have been included. Another limitation is that no information is retrieved from patients’ medical records about when not to intervene and what the reason was for this decision.

In conclusion, with the ODYSSEUS study we aim to confirm the follow-up protocol of the recent ESVS guideline delaying imaging after 5 years if classified in the low risk group and therefore aim to investigate the intervention-free-survival and aneurysm-related mortality for patients with and without yearly imaging surveillance.

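### A patient who leaves the centre unseen tends to be classed as without yearly imaging while later interventions and ruptures go unrecorded, which can flatter that group

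*Protocol article*

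**What the plan says.** **Exposure.** Under Figure 1 in General study design, "the definition of compliance is undergoing imaging surveillance every 16 months since patients in most centres will be rescheduled". Study procedures adds "The time between imaging appointments is calculated to determine whether patients adhere to this studies definition of with yearly imaging surveillance". The primary comparison is between patients with a normal first CTA "who do adhere to our definition of yearly imaging surveillance over a 6-year to 11-year follow-up period" (group A) and those who do not (group B).

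**Sources.** The abstract states "Clinical variables and all follow-up information will be retrieved in extensive data collection from the patient’s medical records", and Study procedures states "Details of all surveillance imaging are obtained from patient medical records and radiology reports". The date of rupture comes from operative reports, radiology reports and progress notes. Only the date of death is verified in an outside register, the municipal database. No outside source is named for interventions or rupture.

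**Endpoint and analysis.** The main study endpoint is expressed as a number of patients with an intervention. Statistical methods adds Kaplan-Meier, log-rank and Cox analyses. Follow-up runs to December 2018.

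**Completeness.** The Discussion concedes "It is also possible that some patients may have transferred to alternative surveillance protocols in different medical centres without our knowledge" and "Attrition bias due to loss to follow-up represents a threat to the internal validity of our cohort study". The same Discussion lists as a strength that "it captures all surveillance visits, long-term outcomes and mortality post-EVAR", and the strengths box after the abstract makes the same claim.

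**The concern.** When a patient's file stops because care has moved elsewhere, two things tend to follow. A long stretch without imaging appears, which points to group B. Later non-fatal events also drop out of view. Exposure and outcome are thus misread together and in a linked way: the unseen time looks both unimaged and event-free.

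The study expects fewer interventions with less follow-up (Study objectives, Discussion), and this error pushes the same way. The plan's existing safeguards do not catch it:

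- The 10% allowance for incomplete data in Sample size and power only raises the number of patients, and more patients do not reduce bias.
- Interventions and ruptures are recorded where present, so an unseen one reads as none rather than as a missing value. The imputation and 15% rules in Statistical methods would not be triggered.

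At stake is a conclusion that reduced surveillance is safe, resting partly on records that simply ended.

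**Working it through.** **1. The plan's own figure.** Sample size and power gives intervention-free rates at 7 years of 75% (yearly imaging) and 82% (no yearly imaging), 90% power and a 0.05 level. The unpooled two-sided formula gives

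n = (0.75×0.25 + 0.82×0.18) × (1.960 + 1.282)² / 0.07² ≈ 719 per group, as stated.

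The planned difference is therefore 7 percentage points, and 719 per group is the base for step 4.

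**2. Model for the distortion.** Assumptions: the true 7-year intervention risk is 25% in both groups, so imaging has no effect; the hazard is constant, at −ln(0.75)/7 = 0.0411 per year; a share f of group B has left the centre; events after departure are unseen and the patient is kept as event-free. The documents give no f.

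Spurious gain for B = f × (0.25 − s), where s is the 7-year risk still recorded among leavers:

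- immediate departure after the first CTA: s = 0
- departure at year 1: s = 1 − exp(−0.0411) = 0.040
- departure uniform over 7 years: s = 1 − 0.25/0.2877 = 0.131

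**3. Results (percentage points in favour of B).**

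| f | Uniform | Year 1 | Immediate |
|---|---|---|---|
| 10% | 1.2 | 2.1 | 2.5 |
| 20% | 2.4 | 4.2 | 5.0 |
| 30% | 3.6 | 6.3 | 7.5 |

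The f needed for the full 7 points is 0.07/0.25 = 28% (immediate), 0.07/0.210 = 33% (year 1) and 0.07/0.119 = 59% (uniform).

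**4. Effect on the test.** With uniform departure and 719 per group, the chance of a significant result favouring B when there is no true difference is 8%, 18% and 36% at f = 10%, 20% and 30%, against a nominal 2.5%.

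**5. From cohort share to f.** If 10% of all patients with a normal first CTA leave unseen, all are labelled B, and the rest split evenly between A and B, leavers make up 0.10/(0.10 + 0.45) = 18% of B. With uniform departure the gain is 0.18 × 0.119, or 2.2 points.

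**6. What censoring does.** Group B was simulated with the step 2 hazard, uniform departure, an assumed death hazard of 0.07 per year and an assumed end of follow-up between 6.9 and 12 years. For f = 10%, 20% and 30%, the 7-year Kaplan-Meier estimate is 0.761, 0.775 and 0.786 when leavers are carried forward as event-free. It is 0.749, 0.751 and 0.751 when they are censored at the true date of departure.

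**7. The opposite error.** The records show the last contact, not the departure date. With no departures at all, a true rate of 0.75, 9 years of follow-up and randomly timed routine contacts, censoring at last contact gives 7-year estimates of about 0.74, 0.70 and 0.65 for mean contact intervals of 1.5, 3 and 5 years. Event-free time after the last routine visit is discarded while time ending in an event is kept.

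**The case against.** The strongest reply is that the distortion needs two rules that the article does not state: that an open interval after the last scan counts as a gap, and that the patient remains at risk after the records stop. Read literally, time between appointments yields no gap when there is no second appointment. The planned survival methods accommodate censoring, and a censoring date is commonly left to a fuller document. This stands as a limit on certainty. It does not remove the point. Judging adherence over 6 to 11 years leans towards treating a stopped file as non-adherence, and a count of patients with an intervention keeps leavers in the denominator. Censoring alone would also leave a patient imaged on time until departure labelled B; it removes the hidden event-free time but not the misassignment.

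A reader might infer more than the documents support:

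- *That every unseen patient goes to B and none to A.* Someone who leaves less than 16 months before follow-up ends can stay in A, and a patient in A may be treated elsewhere as an emergency.
- *That group B is largely made up of such patients, or that the planned 7 points would be an artefact.* No transfer share is given, and 28% is the worst case, with every leaver going straight after the first CTA.
- *That the problem survives any time-varying handling of exposure.* It does so only if follow-up is not also stopped at loss of contact.
- *That all outcomes are equally affected.* All-cause death is largely protected by the register.

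The Discussion does disclose transfer and attrition, but as general limitations. It does not link them to the grouping rule and names no remedy. The objection that censoring at last contact is itself biased against B is correct, and that analysis cannot stand alone.

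**Conclusion.** The point holds as a conditional but directional bias. Exposure and non-fatal outcomes share one source that the article admits may be incomplete, so unseen departure tends both to place a patient in B and to hide later events. If leavers stay in the count or are followed to December 2018, B gains about 1.2 to 2.5 points at f = 10% and 2.4 to 5 points at f = 20%. The full planned 7 points needs f from 28% to 59%, depending on when patients leave. These figures rest on an assumed f, a true 25% risk in both groups, a constant hazard and leavers being kept as event-free. At a low f the effect is modest, but it favours the study hypothesis and a larger sample does not cure it. The claim of complete capture also conflicts with the limitations in the same Discussion.

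**What to change.** In Study procedures and Statistical methods:

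1. Record the date of last documented contact of any kind at the centre.
2. Judge adherence only on imaging due up to that date, so that an open interval after it is not counted as a gap.
3. Report the A versus B comparison of non-fatal endpoints twice: censored at last contact, and carried to death or December 2018. Present the two as bounds, since the first is biased against B where patients are seen mainly when symptomatic, and the second is biased in favour of B.
4. Interpret the safety conclusion in light of both. Neither should act as a veto, because each has a known bias.
5. Reword the claim of complete capture in the strengths box and the Discussion so that it agrees with the stated limitations.

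The cost is one extra variable from records already being extracted, one extra analysis, and fewer person-years with wider intervals in the censored analysis.

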### Background and relevant literature and data

Before initiating the ODYSSEUS study, we conducted a survey among Dutch vascular surgeons to find out if they support the possibility of reducing the frequency of imaging surveillance. In this survey, vascular surgeons reported the main reasons patients did not comply with follow-up visits, that is, they had forgotten the appointment or were prevented by force majeure. Most physicians estimated that less than 10% of their patients had missed one or more follow-up visits post-EVAR. This might be an overestimation of the true adherence to follow-up visits, as these observations are in contrast with a study reporting that only 43% of patients had complete surveillance.^4^

We also asked participating vascular surgeons to upload their standard post-EVAR protocol to investigate if there were differences between centres in the Netherlands. In all centres, imaging took place within the first 3 months after surgery, mostly by CTA. Most centres comply with their own post-EVAR surveillance protocols which have many commonalities with the SVS and ESVS guidelines. Only one centre uses precisely the same post-EVAR surveillance protocol as recommended by the SVS guidelines. Another centre had already reduced follow-up imaging to once every 5 years, using either CTA or DUS as is stated in the new ESVS guidelines.^3^ While vascular surgeons still seem to adhere to their hospital-specific protocol, they do support the need for reducing follow-up by selecting a group of patients for which yearly follow-up can safely be omitted. However, some surgeons indicated that more evidence is needed than is available in the current literature.^6 7^

In studies that have investigated the indications for post-EVAR intervention, it is stated that 61%–98% of interventions were necessary because of symptoms and not because of findings at surveillance imaging. This suggests that post-EVAR surveillance protocols provide no benefit to a large group of patients, as complications occur in between surveillance visits.^8 9^ Imaging surveillance may even lead to unnecessary interventions and it does not appear to be associated with improved survival.^9 10^ We hypothesise that the requirement for routine imaging for patients at low risk can be reduced. However, novel endovascular devices still require more intensive surveillance as the short- and long-term results of those devices remain undetermined.

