### General study design

A multicentre retrospective cohort study in 17 medical centres in the Netherlands. Data will be collected from the medical records of all consecutive patients with AAA who underwent EVAR between January 2007 and January 2012. This selection provides a theoretical length of follow-up of 6–11 years on December 2018. Patients will be divided into three groups: (A) patients without abnormalities at their first postoperative CTA with yearly imaging surveillance, (B) patients without abnormalities at their first postoperative CTA without yearly imaging surveillance and (C) patients with abnormalities at their first postoperative CTA (figure 1). This retrospective design has the advantage of collecting long term follow-up data. The Dutch Dream trial found that the number of interventions starts to rise 4 years after EVAR and the long-term results of the EVAR-1 trial show that EVAR has an early survival benefit but inferior late survival compared to open surgical repair.^13 14^ This is in contrast to the recently published long-term results of the OVER trial in which no difference was observed between EVAR and OSR in the primary outcome of all-cause mortality.^15^ Hence, a prospective study would take approximately 8 to 10 years to gather enough patients with adequate follow-up.

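### The 16-month adherence rule does not say which scans count, so symptom-driven and post-intervention imaging can class some failures of reduced surveillance as yearly surveillance

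*Protocol article*

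**What the plan says.** General study design splits patients with a normal first postoperative CTA into group A (yearly imaging) and group B (no yearly imaging). The text under Figure 1 gives the criterion: "the definition of compliance is undergoing imaging surveillance every 16 months since patients in most centres will be rescheduled" after a missed annual visit. Study procedures gives the only operational rule: "The time between imaging appointments is calculated to determine whether patients adhere to this studies definition of with yearly imaging surveillance". The sentence just before it reads: "Details of all surveillance imaging are obtained from patient medical records and radiology reports". The same section compares patients "who do adhere to our definition of yearly imaging surveillance over a 6-year to 11-year follow-up period" with those who do not, and states no stop at an intervention or other event.

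Indication is recorded: "Date, type, indication and outcome of all postoperative imaging during follow-up are obtained from patient medical records". No sentence links it to the 16-month rule. Statistical methods then compares the groups by Kaplan-Meier curves and the log-rank test.

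**The concern.** The comparison is meant to be routine yearly imaging against less than that. A rule built on intervals between any scans lets the outcome affect the exposure. Take a patient who has dropped out of routine imaging, presents with symptoms 14 months after the last scan, is treated, and is then imaged closely. No gap over 16 months ever appears, so the patient falls in group A. Without the symptoms, the same patient would have passed 16 months unscanned and fallen in group B.

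Such scans should be common around failures, because the background section cites literature in which "61%–98% of interventions were necessary because of symptoms and not because of findings at surveillance imaging". Counting them can only make imaging look denser in patients who fail, which shifts failures from B to A. The study expects fewer interventions with less imaging, so the error favours its hypothesis.

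**Working it through.** **The plan's own figure.** For 75% against 82% intervention-free at 7 years, two-sided alpha 0.05 and 90% power: n = 10.507 × (0.75×0.25 + 0.82×0.18) / 0.07² = 718.6, so 719 per group, as stated. The planned difference is therefore 7 points.

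**Illustration with no true difference.** From the document: 25% intervention by 7 years (used here for both groups), the 16-month limit, and a symptom share within 61%–98%. Assumed: constant hazard h = −ln(0.75)/7 = 0.0411 per year; 80% of interventions symptom-driven; half the cohort has one lapse in routine imaging, with its last routine scan at month L = 12, 24, 36 or 48 (equally likely). S(m) is the probability of no event by month m.

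If a fraction f of the lapsing half moves to A, all of them with an event, then A = (0.125 + 0.5f)/(0.5 + 0.5f) and B = (0.125 − 0.5f)/(0.5 − 0.5f).

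1. *24-month lapse, old schedule resumed, all scans count.* A symptom scan x months into the lapse closes it only if x ≤ 16 and 24 − x ≤ 16, so x lies between 8 and 16. The mean of S(L+8) − S(L+16) over the four L values is 0.0238, and f = 0.8 × 0.0238 = 0.0190. **A 26.4%, B 23.5%: about 3 points.** An independent simulation of this case gave 25.5% against 22.9% with all scans counted, and 24.1% against 24.3% with routine scans only.

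2. *Imaging yearly after the intervention, all scans count.* Any x ≤ 16 now suffices. The mean of S(L) − S(L+16) is 0.0482, and f = 0.8 × 0.0482 = 0.0385. **A 27.8%, B 22.0%: about 6 points.**

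3. *36-month lapse, old schedule resumed.* This needs x ≤ 16 and x ≥ 20, which is impossible, so no one moves. **No bias** (simulation: 25.1% against 24.9%).

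**A second model** planned half the patients at 12-month intervals and half at 18, 24 or 60 months, with 12-monthly scans after an intervention and adherence judged over 96 months. At 18% or 25% risk, counting every scan moved 21%–27% of the sparse group's failures and gave a spurious 6.1 to 10.7 points. Counting only planned surveillance scans over the same window gave −0.4 to +0.5.

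**Does stopping at the first event help?** With fixed groups, any lapsing patient whose event precedes month L+16 is forced into A. The mean of 1 − S(L+16) is 0.1449, so f = 0.1449. **A 34.5%, B 12.3%**; a separate simulation gave about 33% against 12%. In the second model, 6.2 to 10.7 points remain. The 14-month patient also stays in A under this rule, since 14 is less than 16.

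**Does restricting by indication suffice alone?** Not always. Where the schedule restarts at the intervention, the restriction alone, with groups fixed over all follow-up, reversed the gap to 18.1% in A against 30.5% in B.

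**Does updating exposure over time help?** Yes, if symptom scans do not reset the clock: with routine scans only, the A/B rate ratio is 1.0. If current-interval status is used and a symptom scan just before the intervention resets it, the ratio is about 5, because 80% of failures arising in B are moved to A just before they are counted.

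**The case against.** The strongest reply is that the article never says symptom-driven scans count. The compliance definition speaks of imaging surveillance and ties the 16 months to rescheduled annual visits, and the sentence before the operational rule speaks of surveillance imaging. Imaging appointments may well mean those scans only, and a condensed article can leave such detail to the full protocol. This stands in part: a reader might infer a stated inclusion, and the text does not support that. But neither term is defined, the sentence that computes adherence refers only to appointments, and two extractors working independently could both follow the text and group the same patient differently. The article does fix an exposure rule, and that rule omits the variable needed to separate the two kinds of scan.

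A reader might also infer that group B's failures move to A wholesale. They do not: a patient with an earlier gap over 16 months stays in B whatever is scanned later. Nor is scan indication the whole problem. Much of the simulated bias arises because groups are fixed from imaging over all follow-up.

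**Conclusion.** The concern holds as an under-specified exposure rule for the primary comparison. Taken literally, it moves some failures from B to A, in the direction of the hypothesis. For interventions the spurious difference is about 0 (36-month lapse, old schedule resumed), about 3 points (24-month lapse, old schedule resumed), and about 6 points or more if imaging becomes yearly after the intervention, against 7 planned. Lapse length and share, the 80% symptom share, the constant hazard and imaging after an intervention are assumptions, not document figures.

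It is tempting to extend the conclusion to rupture and to aneurysm-related death with its 3% margin. Those effects were not computed and no size can be claimed.

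**What to change.** State in the adherence definition that only scans with a recorded routine-surveillance indication enter the 16-month interval. Name a default class for unclear indications. Say that scans for symptoms, for known complications or after an intervention do not reset the clock.

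Pair this with exposure assigned from information before the event: either a time-updated covariate in the planned Cox model, using status before the symptomatic presentation, or group fixed at a landmark with follow-up counted from there. Do not simply end the assessment at the first event while keeping fixed groups. Repeat the analysis with all scans counted as a sensitivity analysis.

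The cost is a few sentences and a slightly more complex analysis. No new data are needed, since indication is already collected. The main downside is that some scans will have an unclear indication.
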